## Abstract

**Background:**

Football matches induce acute and residual fatigue, impairing neuromuscular, metabolic, and perceptual performance. Hydrogen-rich water (HRW) is a novel intervention with antifatigue and antioxidative properties. The intermittent high-intensity nature of football, which includes frequent accelerations, decelerations, sprints, changes of direction, and physical contacts, imposes substantial demands on both central and peripheral physiological systems. This results in acute fatigue, observable during or immediately after a match, and residual fatigue, which can persist for 24-72 hours post match, depending on the intensity, match context, and recovery strategies.

**Objective:**

This study will investigate the effects of pre-exercise HRW administration versus a placebo on neuromuscular performance, biochemical markers, and perceptual measures of fatigue during a 72-hour recovery after a simulated football match.

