## Methods

### Study Aim

Recognizing the critical role of recovery during intermittent or RSA performance, the anti-fatigue effects of H_2_ and its impact on mitochondrial ATP synthesis support the hypothesis that acute pre-exercise HRW administration, compared with a placebo, may positively affect biochemical, perceptual, and neuromuscular performance variables during a 72-hour period after a simulated football match. This study aims to assess the impact of pre-exercise HRW administration compared with a placebo on biochemical, perceptual, and performance variables within 72 hours after a simulated football match. The specific aims are to assess the impact of pre-exercise HRW administration on acute neuromuscular performance decrement, the impact of pre-exercise HRW administration on acute muscle soreness and the CK levels of players, and the impact of pre-exercise HRW administration on residual muscle fatigue and duration of return to readiness to play.

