### Data Collection

#### Preparation of HRW and Placebo

HRW was obtained in 420 mL plastic-aluminum packs with a gas-tight cap (Aquastamina-R, Nutristamina, Ostrava, Czech Republic). Chemical characteristics of the HRW and placebo were determined using the pH/Oxidation-Reduction Potential/temperature meter (AD14, Adwa Instruments, Szeged, Hungary). The concentration of the dissolved H_2_ was determined using the H_2_Blue reagent (H_2_ Sciences, Henderson, Nevada) using the manufacturer’s guidelines. HRW/placebo characteristics were as follows: pH=7.9/7.7; oxidation-reduction potential −652/+170 mV; and dissolved H_2_ concentration 1.2-1.4/0.0 ppm. The placebo was obtained from the HRW manufacturer and was produced similarly to Aquastamina-R and packed in the same packs.

The participants were instructed to consume three plastic-aluminum packs (1260 mL) 24 hours before the simulated match, two plastic-aluminum packs (840 mL) after finishing the prematch measurement, one plastic-aluminum pack (420 mL) during the first half, and two plastic-aluminum packs (840 mL) consumed after the postmatch measurement. A total of 3780 mL of water was saturated.

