## Discussion

### Anticipated Findings

The recovery period between matches and training sessions may not adequately support critical physiological and psychological recovery processes, such as glycogen repletion, muscle damage, and mental fatigue [33]. Insufficient recovery can decrease performance and elevate injury risk. Understanding the time required for players to regain optimal training readiness is essential for designing effective microcycle plans. For this reason, the study will aim to assess the impact of pre-exercise HRW administration compared with a placebo on biochemical, perceptual, and performance variables after a simulated football match within 72 hours.

RSA performance has been shown to lead to a reduction in oxidative stress and may increase antioxidant protection as a specific training adaptation [34]. Research has shown that increased levels of oxidative stress can result in decreased muscle performance after repeated eccentric exercise [35] as a muscle fatigue manifestation. According to Çakir-Atabek et al [35], HRW consumption may enhance the endogenous antioxidant capacity to respond to the intensity-dependent mitochondrial production of ROS, reduce oxidative stress, and enhance mitochondrial ATP production [17], due to the decrease in lactate accumulation [36]. Botek et al [37] showed that H_2_ application induced an increase in mitochondrial membrane potential, increasing oxygen consumption; cellular ATP, which is an indicator of stimulated oxidative phosphorylation; and mitochondrial ATP production. To protect the quality of the H_2_ against the negative effects of increased ROS/RNS, HRW could increase the mitochondrial efﬁciency and peak muscle power output in later stages of the repeated sprints and delay acute muscle fatigue.

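### The aims call the intervention pre-exercise HRW, but packs are also given during and after the match, so the residual-fatigue aim cannot be answered as worded

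*Protocol article*

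**What the plan says.** All references are to the protocol article.

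**How the intervention is named.** The Objective in the Abstract sets out to study the "effects of pre-exercise HRW administration versus a placebo on neuromuscular performance, biochemical markers, and perceptual measures". In Study Aim, the hypothesis is that "acute pre-exercise HRW administration, compared with a placebo, may positively affect biochemical, perceptual, and neuromuscular performance variables". The general aim and all three specific aims use the same label; the third is to assess "the impact of pre-exercise HRW administration on residual muscle fatigue and duration of return to readiness to play". Anticipated Findings, in the Discussion, restates the purpose as the "impact of pre-exercise HRW administration compared with a placebo on biochemical, perceptual, and performance variables after a simulated football match". The label appears seven times in all: once in the Objective, five times in Study Aim and once in the Discussion.

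**What is given.** Preparation of HRW and Placebo lists "three plastic-aluminum packs (1260 mL) 24 hours before the simulated match", then "two plastic-aluminum packs (840 mL) after finishing the prematch measurement", then "one plastic-aluminum pack (420 mL) during the first half, and two plastic-aluminum packs (840 mL) consumed after the postmatch measurement". It closes with "A total of 3780 mL of water was saturated".

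**When outcomes are measured and how arms are compared.** Study Design places the residual-fatigue tests at 24, 48 and 72 hours. Randomization allocates 1:1 to HRW or placebo. The model in Statistical Analyses has a water factor with two levels and no term for timing of intake.

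**The concern.** A pack drunk in the first half is taken during exercise, and two packs drunk after the postmatch measurement are taken after it. None of the three is pre-exercise in the ordinary sense, so the named intervention and the delivered one differ.

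The difference matters most for the third specific aim. Its outcomes are measured after the post-match packs, and those packs fall at the start of the recovery being studied. Drinking HRW before a match and drinking it afterwards as a recovery measure are different practical recommendations. A report that kept the wording of the aim would credit the first with an effect that may come partly or wholly from the second. The Abstract mentions no intake during or after the match, so someone reading only the Abstract could not detect this.

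**Working it through.** **Inputs** (Preparation of HRW and Placebo; 420 mL per pack)

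| Time of intake | Packs | Volume | Pre-exercise? |
|---|---|---|---|
| 24 hours before the match | 3 | 1260 mL | yes |
| After the prematch measurement | 2 | 840 mL | yes |
| During the first half | 1 | 420 mL | no |
| After the postmatch measurement | 2 | 840 mL | no |
| **Itemised total** | **8** | **3360 mL** | |

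**Step 1: the stated total.** 8 × 420 = 3360 mL, whereas the article states 3780 mL. The gap is 3780 − 3360 = 420 mL, one pack (3780 / 420 = 9). The stated figure is not reproduced. The article does not say whether the total is a slip or a pack is missing from the list. The shares below use the itemised list first; step 5 shows the range if 3780 mL is right.

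**Step 2: share of the whole regimen that is not pre-exercise.** (420 + 840) / 3360 = 1260 / 3360 = 37.5%. The pre-exercise part is 2100 / 3360 = 62.5%.

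**Step 3: share taken after the postmatch test and before the residual-fatigue tests.** 840 / 3360 = 25%. This assumes that the two post-match packs are finished before the 24-hour test, which is the natural reading.

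**Step 4: share that is not pre-exercise before the immediate postmatch test.** By then 1260 + 840 + 420 = 2520 mL has been taken, and only the first-half pack is not pre-exercise: 420 / 2520 = 16.7%.

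**Step 5: the same shares if 3780 mL is correct** (assumption: one unlisted pack, timing unknown).

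| Share | Itemised list | If 9 packs: low | If 9 packs: high |
|---|---|---|---|
| Whole regimen, not pre-exercise | 37.5% | 1260 / 3780 = 33.3% (extra pack before kick-off) | 1680 / 3780 = 44.4% (during or after the match) |
| Post-match packs | 25.0% | 840 / 3780 = 22.2% (extra pack earlier) | 1260 / 3780 = 33.3% (after the test) |
| Before the postmatch test, not pre-exercise | 16.7% | 420 / 2940 = 14.3% (before kick-off) | 840 / 2940 = 28.6% (during the match) |

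**Step 6: what the comparison estimates.** One arm receives HRW at all four intake times and the other receives placebo at all four. Each time point therefore yields one between-arm contrast. At 24, 48 and 72 hours that contrast contains any effect of intake before, during and after the match together. No arm receives HRW before the match only, so nothing in the data isolates the pre-match part. The estimand at these times is the effect of the complete regimen.

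**The case against.** The strongest reply is that this is a matter of labelling and not of validity. Allocation, blinding, time points and model are untouched, and HRW against placebo is a sound comparison of the full regimen. The schedule is disclosed with times and volumes, most of the itemised volume (62.5%) does precede kick-off, and the Conclusions paragraph of the Abstract makes no timing claim. Two of the three specific aims concern acute effects and are little affected. Shares of volume say nothing about shares of effect, and the gap between 3360 and 3780 mL is a separate matter that may be a simple slip.

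Much of this stands. No bias is alleged, the percentages describe intake only, and the ninth-pack ranges are conditional and not needed for the argument. But disclosing the schedule in one section while seven statements elsewhere name a narrower intervention creates a contradiction and does not remove it. A timing word that leaves out more than a third of the itemised dose is more than loose shorthand when one aim concerns recovery and a quarter of that dose is given at the start of recovery. Reading the post-match packs as preceding the later tests does not help either: the aims tie the intervention to the simulated match, and that reading could not cover the first-half pack.

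**Conclusion.** The concern holds and should be fixed. The objective, hypothesis, aims and Discussion name an intervention that the schedule does not deliver, and nothing in the article reconciles the two. By the itemised list, 37.5% of the volume is not pre-exercise (33% to 44% if the stated 3780 mL is right). The consequence is concentrated in the aim on residual fatigue and return to readiness: a difference between arms at 24 to 72 hours can be attributed to the full regimen but not to pre-exercise intake. The acute aims are affected much less. The conclusion does not depend on which total volume is correct, or on how much of any effect each pack contributes.

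**What to change.** - In the Objective, Study Aim and Anticipated Findings, name the intervention as HRW taken before, during and after the match. The Conclusions paragraph of the Abstract and the aim at the end of the Introduction do not use the pre-exercise label and need no change on this ground.
- State that effects at 24, 48 and 72 hours are attributed to the whole regimen.
- In Preparation of HRW and Placebo, state whether 8 or 9 packs are given and when each is taken, so that the regimen named is the regimen drunk.
- If pre-exercise intake is the question truly intended, the schedule itself has to be settled before packs are issued. The article does not show whether that is still possible, since the instructions to participants are already in the past tense; rewording is the dependable remedy.

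**Cost.** The rewording touches three places, plus one clarification of the schedule. Allocation, measurements and model are unchanged. The trial gives up a claim specific to pre-exercise timing, which the design could not have supported at 24 to 72 hours in any case.

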**Methods:**

Using a randomized, double-blinded, placebo-controlled, parallel design, elite junior football players will undergo neuromuscular performance assessments (repeated sprint ability and countermovement jump test). Metabolic fatigue will be measured by creatine kinase level and muscle soreness, rated using a visual analog scale. These assessments will occur at critical time points: immediately post warm-up; directly following the simulated football match to detect acute fatigue; and 24, 48, and 72 hours after training sessions to detect residual fatigue.

**Results:**

Data collection has been scheduled with the clubs to coincide with the beginning of the players’ transition period (ie, at the start of August 2025). The expected duration of data collection, including the initial medical examination, is planned to be 1 month. We anticipate publishing the results in late 2025 or during the first half of 2026.

**Conclusions:**

This study will assess the influence of molecular hydrogen on acute fatigue manifestation and recovery quality during a 72-hour period after a simulated football match. The potential positive effects of molecular hydrogen, such as attenuation of oxidative stress, reduction in muscle damage markers, and accelerated neuromuscular recovery, may contribute to faster restoration of functional capacities. If confirmed, these effects could enhance players’ readiness to return to high-intensity training and optimize the structure of microcycles in competitive periods. Additionally, understanding the recovery dynamics facilitated by HRW may inform evidence-based recovery strategies and support individualized player monitoring frameworks. The possible positive effect of molecular hydrogen would speed up the players’ readiness to train after the match and help protect players against illness and noncontact injuries.

## Introduction

Football is one of the most popular sports worldwide, characterized by its dynamic and intermittent nature that involves a combination of high-speed and high-intensity effort interspersed with periods of low-intensity activity [1]. Understanding the physical and physiological demands of football matches is essential for developing effective training strategies [2]. Given the combined pressures of matches, training sessions, and associated stressors, players must sustain optimal psychological and physical readiness, as well as overall health, throughout the season and tournaments to achieve peak performance. Monitoring players’ readiness and residual fatigue post match is therefore critical for practitioners, as it enables the design of tailored recovery and training plans. This comprehensive approach ensures players maintain consistent performance levels while effectively managing the physical and mental challenges of the sport [3].

Football matches generate significant acute fatigue in players, impacting metabolic, neuromuscular, and perceptual parameters [4]. Recognizing these effects is vital for optimizing recovery strategies and enhancing subsequent performance [5]. The physical demands of modern matches have increased, with players experiencing short recovery periods between games and high neuromuscular strain. This includes a greater frequency of high-intensity running and accelerative actions, which can lead to prolonged residual fatigue [6].

Phosphocreatine availability plays a critical role in intermittent and multiple-sprint performance, with its depletion contributing to performance decline during matches [7]. Prolonged intermittent activity leads to adenosine triphosphate (ATP) and phosphocreatine depletion, reduced neuromuscular excitability, and disruptions in ion homeostasis, which increases reliance on aerobic energy production while inhibiting anaerobic pathways [8,9]. In futsal, for example, 93% of energy production is derived aerobically, with only 5% from anaerobic sources [10]. The relationship between maximal oxygen uptake and repeated sprint ability (RSA) remains ambiguous, with some studies suggesting that RSA performance is more influenced by muscle mitochondrial respiration rates than by maximal oxygen uptake [11].

Mitochondria, through aerobic metabolism, produce reactive oxygen and nitrogen species (ROS/RNS), which serve as both signaling molecules and potential causes of oxidative stress [12]. While moderate ROS/RNS levels are essential for muscle adaptation after training [13], excessive production during repeated sprints can lead to peripheral fatigue and delayed recovery [14]. The body’s antioxidant system works to regulate ROS/RNS levels, but intense exercise can overwhelm this system, demonstrating the delicate balance between energy production and oxidative stress in football [15].

Molecular hydrogen (H_2_) has emerged as a promising intervention for sports performance due to its selective antioxidant properties, targeting ROS/RNS produced during aerobic metabolism [16]. H_2_ also exhibits anti-inflammatory and antiapoptotic effects, along with pH-neutralizing and lactate-reducing capabilities, which can enhance mitochondrial respiration and improve performance in repeated sprint activities [17,18]. Hydrogen-rich water (HRW) has been proposed as a practical hydration strategy during exercise, with evidence suggesting its potential to reduce muscle soreness, perceived exertion, and acute fatigue post exercise [19,20].

Postmatch fatigue significantly affects neuromuscular performance, with assessments like the countermovement jump (CMJ) and RSA tests providing valuable insights [21]. Tools such as the visual analog scale (VAS) are also used to evaluate postexercise muscle soreness, offering reliable measures of discomfort linked to tissue damage [22,23].

Creatine kinase (CK) is a reliable indicator of muscle membrane permeability, as it is predominantly located in skeletal and cardiac muscles [24]. Serving as a biochemical marker of muscle damage, CK is found in both the cytosol and mitochondria of muscle cells. Its levels reflect the extent of muscle recovery and readiness for performance, providing valuable insights into a player’s ability to perform after intense physical exertion [25].

The intervals between matches and training sessions may be insufficient for the restoration and recovery of critical processes such as glycogen replenishment, muscle repair, and mental fatigue. This insufficiency not only decreases the likelihood of achieving optimal performance but also elevates the risk of injury [26]. The timeframe required for a player to regain readiness for training following a match is, therefore, a critical factor in planning microcycles. Accordingly, this study aims to evaluate the impact of a simulated football match on the readiness of young elite football players over a 72-hour recovery period.

## Methods

### Study Aim

Recognizing the critical role of recovery during intermittent or RSA performance, the anti-fatigue effects of H_2_ and its impact on mitochondrial ATP synthesis support the hypothesis that acute pre-exercise HRW administration, compared with a placebo, may positively affect biochemical, perceptual, and neuromuscular performance variables during a 72-hour period after a simulated football match. This study aims to assess the impact of pre-exercise HRW administration compared with a placebo on biochemical, perceptual, and performance variables within 72 hours after a simulated football match. The specific aims are to assess the impact of pre-exercise HRW administration on acute neuromuscular performance decrement, the impact of pre-exercise HRW administration on acute muscle soreness and the CK levels of players, and the impact of pre-exercise HRW administration on residual muscle fatigue and duration of return to readiness to play.

### Study Design

This study protocol was designed according to the 2023 SPIRIT (Standard Protocol Items: Recommendations for Interventional Trials) statement [27]. The experimental study will use a robust research design, adopting a randomized, placebo-controlled, double-blinded, parallel structure (see Figure 1 and Multimedia Appendix 1).

To ensure unbiased results, the administration of HRW and the placebo was randomized and counterbalanced. The investigation will be conducted over a carefully planned 2-week period on a grass football field. During the initial session, participants will be familiarized with the Team^2^Pro Polar suite (1.4.5 version) and briefed on the regulations governing a simulated football match. Before the first measured session, participants will be stratified based on their playing positions (defenders, midfielders, and forwards) and subsequently randomized into either the HRW or placebo groups. Neuromuscular performance will be assessed through measures including the 20-meter repeated sprint test and CMJ. Metabolic fatigue will be measured through CK levels and muscle soreness, as reported using a VAS. These assessments will occur at critical time points: during simulated match day (SMD) immediately post warm-up; directly following the simulated football match to detect acute fatigue; and immediately post warm-up at intervals of 24 (SMD + 1 day), 48 (SMD + 2 days), and 72 (SMD + 3 days) hours after training sessions to detect residual fatigue. The first measurement sessions will be systematically scheduled on Monday afternoons, allowing for a standardized 72-hour recovery period following the last training session. To enhance ecological validity, the simulated match was designed according to official football rules officiated by an experienced referee, comprising two 35-minute halves, with 11 players per team and no substitutions allowed. Regarding intensity regulation, all participants will be instructed to perform at match intensity, which will be monitored using heart rate (HR) data and rate of perceived exertion scores. These measures will indicate consistent physiological workload across participants, supporting the comparability of internal load responses. Environmental conditions (eg, temperature, lighting) will be held constant throughout all testing sessions to reduce external variability.

**Figure 1 figure1:**
[figure not shown]
Overview of the study protocol and labeling of sessions. HRW: hydrogen-rich water; SMD: simulated match day.

### Ethical Considerations

Participants will be informed about the aims of the study, including any risks, discomforts, and benefits, and provide written informed consent. The study was approved by the institutional ethics committee, which follows the Declaration of Helsinki. Participants were not compensated.

### Participants

#### Inclusion and Exclusion Criteria

Czech elite junior male football players will be included. Participants who have at least 10 years of experience, who train at least five times a week with their teams, and who have a match every weekend will be included. Only participants free from injury and medical difficulties will be included in the study. Participants with an illness or injury in the past 3 weeks before the start of measurements and participants who explicitly declined to participate will be excluded.

